### Sample Size

We calculated the sample size based on the primary outcome of MBI scores, which is evaluated at recruitment and at 4, 8, and 12 weeks. The historical mean of the MBI is 73 (SD 25). The study aims to detect a difference of 5 points between the control and intervention groups assuming a correlation of 0.35 between the repeated measurements. The sample size estimated to detect this difference with 80% power and a 5% significance level is 175 participants per group assuming equal allocation between arms. After accounting for 20% attrition, the total sample size required for the study is 450.

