### Statistical Analyses

Participants will be analyzed via an intention-to-treat approach. Participant characteristics will be summarized using median (IQR) or mean (SD) for nonnormally distributed and normally distributed data, respectively, and count and percentage for categorical variables.

Linear mixed-effects model will be used to assess the pattern of change in the primary outcome of the MBI score and secondary outcomes of EQ-5D, 5-time chair stand test (5CST), and joint range over the 12-week follow-up period. A uniform correlation structure will be specified to model the within-subject correlation of these repeated measures. MBI, EQ-5D, 5CST, and joint range of motion will be treated as continuous outcomes. Normality of continuous outcome variables will be assessed through visual inspection methods. If normality assumptions are met, parametric methods will be used; otherwise, a suitable transformation may be performed to address the issue of nonnormality.

As individuals of different age groups have varying body composition, functional capacity, and physiological reserves, there may be differential influences on baseline functional ability and recovery trajectories. To ensure that any potential age-related differences are accounted for, we will first assess the interaction between the age category, treatment groups, and duration of time. We will stratify into age categories, and if statistically meaningful effect modification by age is observed, an age-stratified analysis will then be conducted.

Poisson regression will be used to compare length of stay between intervention and control groups. If there is evidence of overdispersion and/or zero inflation, negative binomial regression or corresponding zero-inflated models will be implemented instead.

Key prognostic factors such as baseline MBI, RDG grouping, and time will be adjusted a priori. The secondary outcome based on 30-day readmission will be compared between the intervention and control group using modified Poisson regression. The effect estimate will be quantified in terms of relative risk and its 95% CI.

For both the primary and secondary outcomes, linear mixed-effects model on the log-transformed scale will be applied if the model assumptions are violated.

Missing data are expected due to the nature of the study and will be handled by imputation.

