The preferred method of imputation will be applied accordingly based on the degree of missingness, such as last observation carried forward.

The cost-effective analysis will evaluate both direct cost savings and cost-effectiveness in terms of quality-adjusted life years (QALYs). To assess direct cost savings, the analysis will evaluate the difference in length of stay at the hospital between the intervention and control group (Table 4). The results will be expressed as mean cost differences between groups. Cost per QALY gained will be evaluated for the cost-effectiveness of the intervention. QALY will be derived using EQ-5D-5L utility scores, and incremental cost-effectiveness ratios (ICERs) will be calculated. The ICERs will be compared to established willingness-to-pay thresholds to determine the cost-effectiveness of the intervention. Sensitivity analyses will be performed to account for uncertainties in cost and QALY estimates. Results will be presented using cost-effectiveness planes and acceptability curve.

**Table 4 table4:** Cost-accounting for the cost-effectiveness analysisa.

Cost category	Cost type	Cost item	Unit of measurement	Source of unit cost	Applicable to
Hardware	Direct	Rebee kits	Per kit per day	Research collaboration agreement	Intervention
Software	Direct	Rebee subscription	Per patient per day	Research collaboration agreement	Intervention
Inpatient care	Direct	Average length of stay	Per patient per day	Electronic medical records	Control and intervention
Manpower	Direct	CRC’s^b^ daily EOM^c^	Per day	Human resource	Intervention

^a^The statistical analysis will be conducted using R (R Foundation for Statistical Computing). All evaluations will be made using 2-side *P* values at the 5% level of significance.

^b^CRC: clinical research coordinator.

^c^EOM: expenditure of manpower.

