## Discussion

### Anticipated Findings and Comparison to Prior Work

To the best of our knowledge, this study is the first to determine the clinical effectiveness and cost-effectiveness of an AI-assisted telerehabilitation device with a structured training program starting from inpatient stay and continued upon discharge via an RCT study design among patients requiring postdischarge rehabilitation care in Singapore. We anticipate that patients receiving the telerehabilitation device and structured training program will demonstrate greater improvement in their functional status, as measured by the MBI, compared to those receiving standard rehabilitation alone. We also expect improvements in joint range, physical performance, and quality of life, with reduction in length of CH stay, lower 30-day readmission rates, and increased cost-effectiveness as compared to usual care alone.

Previous studies have demonstrated that telerehabilitation devices can achieve comparable outcomes compared to conventional rehabilitation services [14,15,22]. However, studies are heterogeneous in terms of the type of intervention and technology used, with varying combinations of in-person or digital personnel required for supervision and execution of the program.

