### Strengths and Limitations

This trial will contribute in several ways to existing knowledge and research regarding telerehabilitation devices and rehabilitation programs. First, it will test user acceptability and compliance with telerehabilitation devices and systems to guide the practicability of application of such devices to routine clinical practice. Second, this will evaluate the cost-effectiveness of such systems versus usual care alone to provide an economic evaluation encompassing resource use, patient-reported quality of life, and physical function improvement. Finally, this will also test whether the addition of such a telerehabilitation system as compared to usual care alone will improve outcomes in terms of functional improvement, length of stay in a CH, and 30-day readmission rates.

There are some limitations to this study. First, it was not possible to blind participants as the intervention involves receiving a physical Rebee device as well as physical sessions to teach the participant about the use of the Rebee device. This might change the behavior and response of participants in the intervention group, causing them to provide more positive outcomes. The difficulty in blinding participants may also increase patient dropout in the control arm as they do not perceive any immediate benefits to them being in the study. Second, the total health care costs calculated in the cost-effectiveness analysis may be underestimated due to omission of certain costings such as postdischarge service use costs and unplanned readmission costs. These costs were excluded because the data on postdischarge service use were collected through patient self-report and could not be verified. On the other hand, there is insufficient information on readmission costs. To minimize inaccuracy, it was decided that these costings will be excluded from the cost-effectiveness analysis. Another limitation is the language barrier, as the Rebee application is only available in English and Mandarin. Considering that Singapore is a multiracial country, this may deter participants who can only read Malay or Tamil from participating in this study. Finally, there is also a potential confounder, which is the digital literacy of participants, which was not assessed in this study. To address this issue, the study team will provide support to participants and caregivers, ensuring that they are able to operate Rebee independently.

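### Imputation is the stated handling of missing data and last observation carried forward its only named method; in recovering patients this could bias the MBI comparison if dropout differs by arm, and the planned mixed model does not need it

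*Protocol article*

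**What the plan says.** Under Statistical Analyses, the protocol article commits to imputation in general terms: "Missing data are expected due to the nature of the study and will be handled by imputation". The next sentence says how the method is to be picked: "The preferred method of imputation will be applied accordingly based on the degree of missingness, such as last observation carried forward". No other imputation method is named. The only sensitivity analyses mentioned concern cost and QALY estimates.

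The same section sets the primary analysis: "Linear mixed-effects model will be used to assess the pattern of change in the primary outcome of the MBI score", with a uniform within-subject correlation and adjustment for baseline MBI, diagnostic group and time. MBI is measured at baseline and at weeks 4, 8 and 12.

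Two statements in the Discussion bear on the consequences. Under Anticipated Findings: "We anticipate that patients receiving the telerehabilitation device and structured training program will demonstrate greater improvement in their functional status". Under Strengths and Limitations: "The difficulty in blinding participants may also increase patient dropout in the control arm as they do not perceive any immediate benefits". The Sample Size section allows 20% attrition overall, with no split by arm.

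**The concern.** LOCF assumes that a patient's score stops changing at the last visit attended. These patients are admitted for rehabilitation and followed while they are expected to improve. A patient lost after week 4 or week 8 is held at partial recovery. A patient lost before week 4 is held at the baseline score for all three follow-up visits. The filled-in values then enter the model as if they had been measured.

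If one arm loses more patients than the other, its mean is pulled down further and the comparison shifts without any treatment effect. If both arms lose the same share, a true effect is diluted. The imputation statement is general, so EQ-5D-5L utilities, and through them the QALYs and the ICER, are exposed in the same way.

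For MBI the step is also unnecessary. A likelihood-based linear mixed model uses every observed visit and is valid when data are missing at random given what the model includes. Tying the method to how much is missing leaves the primary analysis open until the data have been looked at.

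**Working it through.** **1. The plan's own figure.** Inputs from Sample Size: "The historical mean of the MBI is 73 (SD 25"), and an aim to "detect a difference of 5 points between the control and intervention groups assuming a correlation of 0.35 between the repeated measurements", with 80% power and 5% significance (two-sided per the Table 4 footnote).
- Two means: n = 2 × (25 × (1.960 + 0.842) / 5)² = 392.4 per arm.
- Factor for the mean of three follow-ups adjusted for one baseline: (1 + 2 × 0.35)/3 − 0.35² = 0.444.
- 392.4 × 0.444 = 174.3, rounded up to 175 per arm, as stated.
- Attrition: 350 / 0.8 = 437.5, so 438, close to the stated 450 (3 sites × 150).

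This variance structure is used below.

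**2. Assumptions not in the documents.** Mean gain of 9, 13 and 15 points at weeks 4, 8 and 12 in both arms (no true effect). Dropout of 15% ATLAS versus 25% control, or 10% versus 30%; both average the planned 20%. Dropout is unrelated to outcome.

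**3. Gain lost per dropout under LOCF, averaged over the three visits.**
- Lost before week 4: (9 + 13 + 15)/3 = 12.33.
- Lost between weeks 4 and 8: (0 + 4 + 6)/3 = 3.33.
- Lost between weeks 8 and 12: (0 + 0 + 2)/3 = 0.67.
- Evenly spread: (12.33 + 3.33 + 0.67)/3 = 5.44.

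**4. Bias and type I error.** Bias = (control dropout − ATLAS dropout) × gain lost. The article reports 407 recruited, so about 203 per arm: SE = √(2 × 25² × 0.444 / 203) = 1.65. Type I error = Φ(−1.96 + bias/SE) + Φ(−1.96 − bias/SE).

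| Dropout, ATLAS vs control | Timing | Bias (points) | Type I error |
|---|---|---|---|
| 15% vs 25% | evenly spread | 0.10 × 5.44 = +0.54 | 6.2% |
| 15% vs 25% | all between weeks 4 and 8 | 0.10 × 3.33 = +0.33 | 5.5% |
| 15% vs 25% | all before week 4 | 0.10 × 12.33 = +1.23 | 11.6% |
| 10% vs 30% | evenly spread | 0.20 × 5.44 = +1.09 | 10% |
| 10% vs 30% | all between weeks 4 and 8 | 0.20 × 3.33 = +0.67 | 6.9% |
| 10% vs 30% | all before week 4 | 0.20 × 12.33 = +2.47 | 32% |

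Simulation of the evenly spread and early patterns (4,000 trials, ANCOVA on the mean of the LOCF-filled visits) gave type I errors of 6% and 9% for evenly spread dropout, and 11.6% and 30% for early dropout. Swapping the dropout rates between arms reverses the sign of the bias.

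**5. Equal dropout of 20%.** With no true effect the bias is zero. A constant true effect of 5 points shrinks to 5 × (1 − 0.20) = 4.0 if all loss is before week 4, and to 5 × (1 − 0.20/3) = 4.67 if evenly spread.

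**6. Second check with a different recovery curve.** Final gains of 5 to 20 points were assumed, with 50%, 80% and 100% reached at weeks 4, 8 and 12. With evenly spread dropout the week-12 bias is +0.28 to +1.13 points (15% vs 25%) and +0.57 to +2.27 points (10% vs 30%). If all loss is early the upper ends are +2.0 and +4.0. At a 15-point gain (600 simulated trials, 219 per arm), LOCF rejected a true null in about 7% and 12% of runs. The same model on observed visits alone rejected in about 5%, with estimates within about 0.1 of zero. Monte Carlo error near 5% is √(0.05 × 0.95/600) ≈ 0.9 percentage points. With equal dropout LOCF rejected in 4.5% of runs, so the inflation seen comes from the shift in means.

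**The case against.** The best reply is that the article cites LOCF only as an example, leaving other methods open, and that thresholds, missing-data assumptions and sensitivity analyses belong in an analysis plan that is not shown. Most of that stands, and the absence of such detail is not the point here. What remains is in the text itself: imputation is the stated handling, the one method offered suits this population badly, and it sits beside a model that does not need it.

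Several stronger readings are tempting, but the documents do not support them.

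- That the plan predicts more control dropout, so the bias must favour ATLAS. The wording is only that "The difficulty in blinding participants may also increase patient dropout in the control arm", with no rate. The voucher at study completion goes to participants in both arms and may support retention in each.
- That all dropouts are frozen at pre-recovery scores. This is true only of those lost before week 4. The article puts the usual inpatient stay at around 3 to 4 weeks, so much of that window is spent in hospital, where loss is less plausible. If all loss falls between weeks 4 and 8, the type I error is 5.5% or 6.9%.
- That a 30% type I error should be expected. It needs a threefold dropout imbalance, all of it before week 4.
- That the method will be picked with knowledge of arm. The article calls the trial unblinded, but the amount of missing data can be an overall rate, and nothing says that arm or outcome data inform the choice.
- That utilities would be carried past death. The article does not say how deaths enter the QALYs.

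Dropouts who are deteriorating would also change the picture: LOCF could then flatter them, and a missing-at-random model could be biased too. That argues for a sensitivity analysis and does not support LOCF.

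**Conclusion.** The point holds in conditional form and should be fixed. LOCF in a recovering population could bias the MBI comparison in favour of ATLAS if control dropout is higher, against ATLAS if ATLAS dropout is higher, and dilutes a true effect if dropout is equal. At a 10-percentage-point imbalance and the gains assumed above, the bias is about +0.5 points (11% of the 5-point target) with evenly spread dropout and about +1.2 points (25%) if all loss is early, with type I error of about 6% and 12%. At 10% versus 30% the bias is about +1.1 to +2.5 points.

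Confidence is high that LOCF is a poor choice here and unnecessary for MBI. It is lower for direction and size, because the recovery gain, dropout by arm and dropout timing are all assumed.

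**What to change.** 1. Delete LOCF and the rule that picks the method by how much is missing.
2. State that the primary MBI analysis is the planned likelihood-based linear mixed model on all observed visits, without imputation, assuming missing at random.
3. Add a sensitivity analysis: multiple imputation by arm, with a delta-adjusted or control-based tipping point. This also brings in patients with no follow-up visit, who contribute nothing when baseline MBI is a covariate.
4. For the QALY and ICER analysis, use multiple imputation by arm for missing EQ-5D-5L utilities and for any missing costs.
5. The article reports that data collection finished in December 2025 and that analysis has begun. Record the change with a date and rationale before results by arm are seen. If they have already been seen, say so.

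The cost is revised wording and a little extra analysis. No new data are needed.

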### Outcome Measures

The primary outcome is functional status measured over 12 weeks. Functional status will be measured using modified Barthel index (MBI), a 100-point ordinal scale for the assessment of a patient’s functional state. The MBI assesses activities of daily living over 10 domains comprising transfers, ambulation, stair climbing, bathing, dressing, toileting, bowel control, bladder control, personal hygiene, and feeding [29].

Secondary outcomes include physical performance, quality of life, length of stay in CH, 30-day readmission rates, and cost-effectiveness over 12 weeks. Patients who are admitted under RDG total knee replacement will have an additional outcome measure of joint range. The outcome measures as well as the method of measurement are listed in Table 3. Health care cost will be calculated from electronic medical records and supplemented with survey data regarding the number of DRC or home therapy sessions attended, manpower hours to train patients to use Rebee, costs of Rebee software and hardware, and use of outpatient community services (eg, day care center, home nursing, housekeeping, and meals on wheels). The tools to be used in this study to measure the outcomes are validated and implemented in routine clinical care.

**Table 3 table3:** Primary and secondary outcome measures.

Variables			Data source, method of measurement, and definitions		Time points
Primary outcome					
	Functional status	Survey: MBI^a^. To establish the degree of independence from any help. A score from 0- 100 using the MBI questionnaire, with 100 being fully ambulant without any help.		Baseline and 4, 8, and 12 weeks	
Secondary outcomes					
	Joint range	Measurement using goniometer on affected knee. Active and passive range of motion (flexion and extension) of affected knee.		Baseline and 4, 8, and 12 weeks	
	Physical performance	Measured by performing 5CST^b^. Measures the time taken to complete 5 sit to stands (in seconds)		Baseline and 4, 8, and 12 weeks	
	Quality of Life	Survey: EQ-5D-5L		Baseline and 4, 8, and 12 weeks	
	Length of stay	Electronic medical records		Date of discharge from CH^c^ minus date of randomization	
	30-day readmission rates	Electronic medical records		12 weeks	
	Direct health care cost	Electronic medical records: cost of inpatient stay		12 weeks	
	Direct health care cost	CRC’s^d^ daily expenditure of manpower		4, 8, and 12 weeks	
	Direct health care cost	Rebee costs: software and hardware		12 weeks	

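### The direct-cost-savings rule names only length of stay, although Tables 3 and 4 class the Rebee and manpower costs, which Table 4 charges to the intervention arm only, as direct costs

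*Protocol article*

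**What the plan says.** The economic paragraph under Statistical Analyses announces two outputs, a direct cost saving and a cost per QALY. For the first it says: "To assess direct cost savings, the analysis will evaluate the difference in length of stay at the hospital between the intervention and control group", with a reference to Table 4. The next sentence adds: "The results will be expressed as mean cost differences between groups". The second output is an ICER, with QALYs derived from the EQ-5D-5L.

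Direct cost is set out more widely elsewhere:

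- The text under Outcome Measures includes in health care cost "manpower hours to train patients to use Rebee, costs of Rebee software and hardware".
- Table 3 has three rows for direct health care cost: inpatient stay, the research coordinator's manpower, and "Rebee costs: software and hardware".
- Table 4 has four items, all typed as direct. They are Rebee kits ("Per kit per day"), the "Rebee subscription", inpatient length of stay, and coordinator manpower. Length of stay applies to both arms; the other three apply to the intervention arm only.

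The Strengths and Limitations section names the costs left out of the economic analysis, namely postdischarge service use and unplanned readmissions. The costs of ATLAS are not among them.

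**The concern.** The rule names one of the four items that the article itself calls direct. It is the item that the trial's hypothesis expects ATLAS to reduce. The three items it does not name are the ones that ATLAS adds. If an analyst follows the sentence to the letter, the result is an inpatient cost offset presented as a direct cost saving.

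Two things are at stake. First, a modest reduction in stay could be reported as a saving when the programme costs more than the bed-days it frees. Second, if the ICER uses all of Table 4, the same trial could report a saving in one place and a positive incremental cost in another. The article intends its economic findings to inform policymakers, and readers told which costs were excluded would reasonably take a reported saving to be net of the intervention's own cost.

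**Working it through.** The article states no cost figure, so there is nothing to reproduce. The check compares the passages and then works out a break-even.

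**Step 1. The passages side by side.**

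| Item | Direct in Table 3? | Direct in Table 4? | Arms in Table 4 | Named in the savings rule? |
|---|---|---|---|---|
| Inpatient stay | yes | yes | both | yes |
| Rebee hardware (kits) | yes | yes | intervention | no |
| Rebee software (subscription) | yes | yes | intervention | no |
| Coordinator manpower | yes | yes | intervention | no |

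The tables agree with each other. The sentence is the odd one out, apart from its reference to Table 4.

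**Step 2. Direction.** Let d be the mean inpatient days saved per patient, c the cost of one inpatient day, D the device-days per intervention patient, and k the mean daily ATLAS cost (kit, subscription and manpower, averaged over D).

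- Gross saving = d × c
- Net saving = d × c − D × k
- Gross − net = D × k

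The control arm carries none of the three omitted items and k cannot be negative. On the literal reading the discrepancy therefore has one sign only, in favour of ATLAS.

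**Step 3. Break-even.** Net saving is zero when k/c = d/D. The device is retrieved at week 12 (Structured Program), so D is at most 12 × 7 = 84. The values of d are assumptions; the article gives no expected reduction, only a usual stay of around 3 to 4 weeks (Usual Care).

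- d = 1: 1/84 = 1.19%
- d = 2: 2/84 = 2.38%
- d = 3: 3/84 = 3.57%

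Above these fractions of an inpatient day's cost, a gross saving is a net cost.

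**Step 4. Net result in inpatient-day equivalents**, d − 84 × (k/c), for assumed k/c:

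| Gross saving d | k/c = 1% | k/c = 2% | k/c = 5% |
|---|---|---|---|
| 1 | +0.16 | −0.68 | −3.20 |
| 2 | +1.16 | +0.32 | −2.20 |
| 3 | +2.16 | +1.32 | −1.20 |

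For example, with d = 1 and k/c = 2%, the literal rule reports a saving worth 1.00 inpatient day. An ICER built on all four items would carry an incremental cost of 84 × 0.02 − 1 = 0.68 inpatient days.

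**Step 5. Sensitivity to device-days.** 84 is an upper limit. Participants may stop using the device on request, and the article does not say when daily charging ends. With D = 42 the break-even fractions double; for d = 1 it is 1/42 = 2.38%.

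**The case against.** The best case against is that the sentence is condensed, not wrong. It never says that length of stay is the only component. It refers to Table 4, which prices all four items, and the following sentence promises cost differences between groups, not differences in days. Table 4 is titled as the accounting for the cost-effectiveness analysis, and the article puts both outputs under that analysis: "The cost-effective analysis will evaluate both direct cost savings and cost-effectiveness in terms of quality-adjusted life years (QALYs"). The ATLAS costs do not appear among the declared exclusions. On this view the full analysis plan, which is not shown, would assemble the net figure.

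Much of this stands. A net reading is available, so a gross saving is a consequence of the literal wording and not an established feature of the analysis. What does not stand is the suggestion that this is merely detail left to another document. The article states a rule, the rule names one component, and two of its own tables define the quantity more widely. The two readings can differ in sign.

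A reader might go further and infer that the trial's cost-effectiveness conclusion is biased towards ATLAS. The documents do not support that. The article judges cost-effectiveness by comparing the ICER with willingness-to-pay thresholds, and Table 4 supplies the ATLAS costs for that purpose. Nor do they support any claim about how large the discrepancy is in money or relative to its sampling error, since they give neither unit costs nor a standard deviation for length of stay.

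**Conclusion.** The point holds as a conflict of definition. The direct-cost-savings rule names length of stay alone, while Tables 3 and 4 class the Rebee and manpower costs as direct, with Table 4 charging them to the intervention arm only. If the rule is followed literally, the reported saving is gross of ATLAS costs, can err only in favour of ATLAS, and may contradict the incremental cost in the ICER. If it is read through Table 4 as net, none of this arises.

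The size in money cannot be computed. The break-even fractions of about 1.2%, 2.4% and 3.6% for 1, 2 and 3 days saved show only that a small daily ATLAS cost would be enough to reverse the sign. They rest on assumed reductions in stay and on the full 84 device-days for every intervention patient; fewer device-days raise them.

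The conflict should be settled before costs are compared by arm. The article reports that data collection is complete and analysis is underway.

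**What to change.** Replace the sentence under Statistical Analyses with a definition along these lines: the direct cost difference is the mean per-patient difference between arms in the sum of all four Table 4 items (inpatient days, Rebee kits, Rebee subscription and coordinator manpower), reported with its 95% CI, and the same incremental cost is the numerator of the ICER. If a figure based on length of stay alone is also shown, label it as an inpatient cost difference, gross of ATLAS cost, and place the net figure beside it.

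The cost is one sentence. No new data are needed, because Table 4 already names the source of each unit cost. The downside for the sponsor is that, compared with the literal rule, the reported saving becomes less favourable.

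### Incremental QALYs have no stated adjustment for baseline EQ-5D-5L utility; adding it is free and would make the ICER more precise

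*Protocol article*

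**What the plan says.** All statements are in the protocol article.

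- **Outcome Measures, Table 3.** Quality of life is "Survey: EQ-5D-5L", measured at "Baseline and 4, 8, and 12 weeks". The 5CST and knee joint range have the same four time points.
- **Statistical Analyses, repeated measures.** A linear mixed-effects model is planned for MBI and for the "secondary outcomes of EQ-5D, 5-time chair stand test (5CST), and joint range over the 12-week follow-up period". On the covariance: "A uniform correlation structure will be specified to model the within-subject correlation of these repeated measures".
- **Statistical Analyses, covariates.** "Key prognostic factors such as baseline MBI, RDG grouping, and time will be adjusted a priori". MBI is the only baseline score named, and the wording gives examples rather than a closed list.
- **Statistical Analyses, economics.** "QALY will be derived using EQ-5D-5L utility scores, and incremental cost-effectiveness ratios (ICERs) will be calculated". Uncertainty is addressed by "Sensitivity analyses will be performed to account for uncertainties in cost and QALY estimates", with cost-effectiveness planes and an acceptability curve. No regression model or covariate is given for QALYs.
- **Randomization and Blinding.** Recruitment site is the only stratification factor, so the design does not balance baseline utility.

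**The concern.** QALYs are a separate step outside the mixed model, so whatever use that model makes of baseline EQ-5D does not automatically reach them. A QALY computed as the area under the utility curve contains the baseline utility. A chance difference between arms at baseline therefore enters twice: directly, as the first point of the area, and indirectly, because people with higher baseline utility tend to have higher follow-up utility.

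Over 12 weeks any plausible QALY gain is small in absolute terms, and the QALY difference is the denominator of the ICER. Cost-effectiveness is part of the trial's stated objective. Precision that could be had from data already collected would be given up if the text were followed literally.

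**Working it through.** **1. The plan's own use of a baseline.** Sample Size gives SD 25, a difference of 5 points, correlation 0.35, 80% power, 5% significance (two-sided per the note to Table 4) and 175 per group. With one baseline and three follow-ups under uniform correlation, and adjustment for the outcome's own baseline:

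n = 2 × [25 × (1.960 + 0.842)/5]² × [(1 + 2×0.35)/3 − 0.35²] = 392.44 × 0.4442 = 174.3, so 175.

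This reproduces the stated figure. Without the baseline term the factor is 0.5667 and n is 223; 175 per group would then give 70% power. The sample size for MBI is thus consistent with own-baseline adjustment, and the question is whether the same is done for QALYs.

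**2. Inputs for the QALY calculation.**

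- From the article: measurements at 0, 4, 8 and 12 weeks; uniform correlation; 407 recruited (Results), so about 203 per arm.
- Assumed, because the article does not give them: utility SD 0.25 (range 0.15 to 0.35); utility correlation ρ of 0.35 (the MBI value, borrowed) or 0.6; a utility gain of 0.03 at weeks 4, 8 and 12 (0.05 as an alternative).

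**3. Formulas.** The trapezoid weights are (0.5, 1, 1, 0.5) × 4/52 years.

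- Carry-through of baseline imbalance: (0.5 + 2.5ρ) × 4/52 QALY per utility unit. The direct part is 0.5 × 4/52 = 0.038; the rest comes through correlation.
- QALY variance: (4/52)² × SD² × (2.5 + 6.5ρ).
- Adjusted/unadjusted variance: 1 − (0.5 + 2.5ρ)²/(2.5 + 6.5ρ).
- SE of the baseline difference: SD × √(2/203) = 0.0248 at SD 0.25 (0.0149 at 0.15, 0.0347 at 0.35).
- QALY value of a sustained 0.03 gain: 0.03 × 2.5 × 4/52 = 0.0058 (0.0096 for a gain of 0.05).

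**4. Results.**

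| ρ | Carry-through | QALY shift for a 1-SE imbalance, SD 0.25 (SD 0.15 to 0.35) | Share of 0.0058 at SD 0.25 | Adjusted/unadjusted variance |
|---|---|---|---|---|
| 0.35 | 1.375 × 4/52 = 0.106 | 0.0026 (0.0016 to 0.0037) | 45% | 1 − 1.891/4.775 = 0.604 |
| 0.6 | 2.0 × 4/52 = 0.154 | 0.0038 (0.0023 to 0.0053) | 66% | 1 − 4/6.4 = 0.375 |

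Against a gain of 0.05 the shares are 27% and 40%. At ρ = 0.35 and SD 0.25, the SE of the QALY difference is 0.0042 unadjusted and 0.0032 adjusted.

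**5. Could an imbalance cancel the assumed gain?** That takes 0.00577/0.00262 = 2.2 SE at ρ = 0.35 (one-sided chance about 1.4%) or 0.00577/0.00382 = 1.5 SE at ρ = 0.6 (about 6.5%).

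**6. EQ-5D, 5CST and joint range.** If these models used post-baseline values only, with baseline MBI as the sole baseline covariate, replacing it with the outcome's own baseline would leave 0.79 to 0.85 of the variance of the follow-up mean at ρ = 0.35. This assumes a correlation of 0.2 to 0.6 between baseline MBI and the outcome's own baseline. The article does not say whether baseline is a covariate or a modelled time point.

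**The case against.** The strongest reply is that the article is silent, and silence is not a plan to compare QALYs unadjusted. It states neither an adjusted nor an unadjusted contrast, and the covariates of a QALY regression are commonly left to an analysis plan or health-economics plan that is not shown. The covariate list is open, so own-baseline terms are not excluded; baseline MBI may be named simply because it is the primary outcome's own baseline. All of this stands, and it is why the point is an improvement and not a contradiction or error.

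Two stronger readings are tempting, and the documents support neither.

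- *That ordinary chance imbalance reverses the ICER.* On the assumptions above, a 1-SE imbalance is 45% to 66% of a 0.03 gain and does not change its sign. The imbalance is random, so it costs precision and affects the realised estimate without systematic bias. The SE stays large against the effect even after adjustment, and the planned plane and acceptability curve would display that uncertainty.
- *That EQ-5D, 5CST and joint range lose precision under the plan.* Baseline is one of their four listed time points. If it is modelled as such, the group-by-time contrast already uses each outcome's own baseline, and no loss is established.

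What the reply does not remove is that the described route from utilities to QALYs to ICERs contains no baseline-utility term, and that taking it literally gives the less precise estimate.

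**Conclusion.** A free improvement of minor to moderate weight, confined mainly to QALYs and the ICER. If QALYs are compared without baseline utility, the estimate remains unbiased over randomizations, but its variance is larger than it need be: adjustment removes about 40% at correlation 0.35 and 62% at 0.6.

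The mechanism and the variance ratios rest on the article's visit schedule, its uniform correlation structure and a correlation borrowed from MBI. The absolute QALY shifts rest also on the assumed utility SD, and the percentage shares on the assumed gain as well; at correlation 0.35 the share of a 0.03 gain runs from 27% to 64% over SD 0.15 to 0.35 (0.00157/0.00577 to 0.00367/0.00577). For EQ-5D, 5CST and joint range the point is conditional on models that use post-baseline values only.

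**What to change.** State in the analysis plan that incremental QALYs will be estimated by regression on arm and baseline EQ-5D-5L utility, with RDG grouping and with site as the stratification factor. State also that these adjusted increments feed the ICER, the cost-effectiveness plane and the acceptability curve.

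Add one sentence on how baseline enters the mixed models. If they use post-baseline values only, each of EQ-5D, 5CST and joint range should have its own baseline as covariate rather than baseline MBI alone. If baseline is a modelled time point, saying so is enough.

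The cost is a few lines of wording; every baseline is already collected. Because data collection is complete and analysis is under way, the wording should be dated and fixed before QALYs are compared between arms.
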